**Determinants of change**				
Team climate	Team climate inventory	1 (T0 (before) measurement)	−3 months	Professional
Patients safety culture	Hospital survey on patient safety culture	1 (T0 (before) measurement)	−3 months	Professional
**Barriers and facilitators of guideline adherence**	Questionnaire	1 (before the start of the implantation period in the concerning group of hospitals) *N* ≥ 7 (at least one surgeon, anesthesiologist, OR, anesthesia, recovery, and ward nurse, and ICU employee)	Variable (depending on the start of the implementation period)	Professional

The rationale for these secondary outcomes is based on a prioritization procedure by 16 perioperative health-care professionals in the nine participating hospitals: they were invited to list ten outcomes with the highest clinical relevance to perioperative care.

#### Definitions of outcomes at patient level

We define a complication as an unintended and unwanted event or state during or following medical treatment that has an unfavorable effect on the health of the patient to such an extent that adjustment of the medical treatment is necessary or irreparable harm has occurred [29]. Postoperative wound infections are divided into superficial and deep wound infections, with one of the following three symptoms present: pain and or sensitivity, local swelling, redness and or warmth [30]. Postoperative mortality is the death of a patient as the result of any perioperative complication. Length of hospital stay is defined as the time period in days between admission and discharge. An unplanned reoperation is any secondary surgical procedure required as a result of a complication directly or indirectly related to the index operation [31]. A non-elective readmission is an unintended, acute readmission from the index admission [32]. A readmission includes at least one overnight stay. An unscheduled transfer to the ICU is identified when an admission to the ICU department has not been ordered preoperatively. All these data are obtained from the hospital information systems.

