**Methods/design:**

This is a stepped wedge cluster randomized trial including nine representative hospitals across The Netherlands. Hospitals are stratified into three groups according to hospital type and geographical location and randomized in terms of the period for receipt of the intervention. All adult surgical patients meeting the inclusion criteria are assessed for patient outcomes. The implementation strategy includes education, audit and feedback, organizational interventions (e.g., local embedding of the guidelines), team-directed interventions (e.g., multi-professional team training), reminders, as well as patient-mediated interventions (e.g., patient safety cards). To tailor the implementation activities, we developed a questionnaire to identify barriers for effective guideline adherence, based on (a) a theoretical framework for classifying barriers and facilitators, (b) an instrument for measuring determinants of innovations, and (c) 19 semi-structured interviews with perioperative key professionals. Primary outcome is guideline adherence measured at the hospital (i.e., cluster) and patient levels by a set of perioperative Patient Safety Indicators (PSIs), which was developed parallel to the perioperative guidelines. Secondary outcomes at the patient level are in-hospital complications, postoperative wound infections and mortality, length of hospital stay, and unscheduled transfer to the intensive care unit, non-elective readmission to the hospital and unplanned reoperation, all within 30 days after the initial surgery. Also, patient safety culture and team climate will be studied as potential determinants. Finally, a process evaluation is conducted to identify the compliance with the implementation strategy, as well as an economic evaluation to assess the costs. Data sources are registered clinical data and surveys. There is no form of blinding.

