### Outcome measures

Several outcomes are measured at the hospital (i.e., the cluster) and the patient levels (Table 3). The primary outcome measure is guideline adherence according to the PSIs as defined in the national indicator set. This set comprises nine indicators on the processes and structures of care [18]. Secondary (patient) outcomes are in-hospital complications (with particular attention to postoperative wound infections) and hospital mortality, as well as length of hospital stay (LoHS), unscheduled transfer to the intensive care unit (ICU), non-elective hospital readmission, and unplanned reoperation, which are derived from a maximum period of 30 days after the initial surgery.

**Table 3 Tab3:** **Methods and instruments for measuring the effects of a multifaceted implementation strategy to implement the Dutch national perioperative safety guidelines**

**Outcome variable**	**Data source (type of measurement)**	**Frequency of measurement and sample size per measurement**	**Moment of measurement**	**Unit of analysis**
**Primary outcome** (guideline adherence measured by an indicator set of nine process and structure indicators)				
Completion of the total STOP bundle (seven separate stop moments in the perioperative care process), % patients	Retrospective patient record review in the hospital information systems	4 (T0 (before), T1, T2, T3 (after) measurement) *N* = 1,800	−3 months, +4 months, +11 months and +18 months	Patient
Availability of a protocol on antibiotic use	Short questionnaire on the underlying items of the structure indicators	4 (T0 (before), T1, T2, T3 (after) measurement) *N* = 1	−3 months, +4 months, +11 months and +18 months	Hospital
Timely administration of antibiotic prophylaxis, % patients	Retrospective patient record review in the hospital information systems	4 (T0 (before), T1, T2, T3 (after) measurement) *N* = 1,800	−3 months, +4 months, +11 months and +18 months	Patient
Availability of a protocol on anticoagulant use	Short questionnaire on the underlying items of the structure indicators	4 (T0 (before), T1, T2, T3 (after) measurement) *N* = 1	−3 months, +4 months, +11 months and +18 months	Hospital
Availability of a protocol on responsibilities regarding maintenance of medical equipment	Short questionnaire on the underlying items of the structure indicators	4 (T0 (before), T1, T2, T3 (after) measurement) *N* = 1	−3 months, +4 months, +11 months and +18 months	Hospital

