**Secondary outcomes**				
Complications (in-hospital), % patients	Retrospective patient record review in the hospital information systems	4 (T0 (before), T1, T2, T3 (after) measurement) *N* = 1,800	−3 months, +4 months, +11 months and +18 months	Patient
Postoperative wound infections (in-hospital), % patients	Retrospective patient record review in the hospital information systems	4 (T0 (before), T1, T2, T3 (after) measurement) *N* = 1,800	−3 months, +4 months, +11 months and +18 months	Patient
Postoperative mortality (in-hospital), % patients	Retrospective patient record review in the hospital information systems	4 (T0 (before), T1, T2, T3 (after) measurement) *N* = 1,800	−3 months, +4 months, +11 months and +18 months	Patient
Length of hospital stay, number of days	Retrospective patient record review in the hospital information systems	4 (T0 (before), T1, T2, T3 (after) measurement) *N* = 1,800	−3 months, +4 months, +11 months and +18 months	Patient
Unscheduled transfer to the ICU (within 30 days after the initial surgery), % patients	Retrospective patient record review in the hospital information systems	4 (T0 (before), T1, T2, T3 (after) measurement) *N* = 1,800	−3 months, +4 months, +11 months and +18 months	Patient
Non-elective hospital readmission (within 30 days after the initial surgery), % patients	Retrospective patient record review in the hospital information systems	4 (T0 (before), T1, T2, T3 (after) measurement) *N* = 1,800	−3 months, +4 months, +11 months and +18 months	Patient
Unscheduled reoperation (within 30 days after the initial surgery), % patients	Retrospective patient record review in the hospital information systems	4 (T0 (before), T1, T2, T3 (after) measurement) *N* = 1,800	−3 months, +4 months, +11 months and +18 months	Patient

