With respect to the limitations of the study, the power of the stepped wedge cluster randomized trial design decreases if the treatment gradually reaches its expected effect after one or more time intervals after the intervention [22]. The greater the delay in the intervention effect, the greater the loss of power. This can be a problem in the third group of hospitals as the effect measurement is conducted immediately after the implementation phase (the last group starts with the implementation activities after T2). It is therefore important to make the time intervals sufficiently long so that the full intervention effect is realized in a single interval. The power can also be partly, but not completely, restored by adding additional measurement periods onto the end of the trial. Another limitation of this study is the costs of the frequent data collection. If the necessary data are not easy to collect and time-consuming, the cost of data collection is substantial. A further limitation is due to the fact that our sample size is calculated for the primary outcome measure. Power may be too low to draw conclusions about the effect of guideline adherence on perioperative patient safety. Blinding of the intervention is not possible as the trial is designed to evaluate an implementation intervention to change professional behavior in the real hospital setting. Outcomes assessment was not blind either, but as indicators are rather objective (e.g., is a protocol for anticoagulant use available or not), it is unlikely that they are influenced by the assessment.

Overall, knowledge of the results of this study will improve the implementation success of the perioperative guidelines. It is expected that better adherence to the perioperative safety guidelines will improve the safety of perioperative care.

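### Mortality counts only deaths attributed to a complication, in an unblinded record review, and the observation windows of the secondary outcomes are stated inconsistently

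*Protocol article*

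**What the plan says.** Definitions of outcomes at patient level restricts mortality by cause: "Postoperative mortality is the death of a patient as the result of any perioperative complication". The same section defines length of stay as the time from admission to discharge and takes all patient-level data from the hospital information systems. Under Data sources, two researchers extract the data retrospectively from medical records. The Discussion concedes the lack of blinding and defends it: "Outcomes assessment was not blind either, but as indicators are rather objective". Its example is whether a protocol is available.

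The windows are given in three places:

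- Table 3 labels three outcomes in-hospital with no day limit: "Complications (in-hospital), % patients", "Postoperative wound infections (in-hospital), % patients" and "Postoperative mortality (in-hospital), % patients". Three others have a 30-day window, for example "Unscheduled transfer to the ICU (within 30 days after the initial surgery), % patients"; readmission and reoperation are worded alike. Length of stay has no window.
- The Abstract opens its list of secondary outcomes with the word in-hospital and closes the same sentence with "non-elective readmission to the hospital and unplanned reoperation, all within 30 days after the initial surgery".
- Outcome measures speaks of in-hospital complications and hospital mortality, adds length of stay, ICU transfer, readmission and reoperation, and ends "which are derived from a maximum period of 30 days after the initial surgery". It is unclear whether this covers the whole list or only its second half.

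**The concern.** Death from any cause needs no judgement. Death resulting from a complication does, and the records behind that judgement may change with the intervention: a morbidity and mortality registration and a wound-infection surveillance system are among the primary indicators in Table 3 that the strategy is meant to improve. If deaths are attributed to complications more or less readily in the intervention phase, the mortality comparison moves with no change in risk.

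The windows raise two further matters. Two people working from different parts of the article could count the same patient differently. And an in-hospital window closes at discharge, while length of stay is itself an outcome. If the strategy changes stay, it changes the time during which infections, complications and deaths can be counted.

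At stake is the second research question, whether patient safety improves with better adherence. The primary adherence outcome is not involved.

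**Working it through.** **The plan's own figures.** 50 patients × 9 hospitals × 4 measurements = 1,800, as stated. With the Hussey and Hughes variance (9 clusters, 3 crossing per step, 50 per cluster-period, 50% versus 65%, two-sided alpha 0.05), power is about 0.92 to 0.98 at an ICC of 0.1 or 0.3, depending on the variance convention. This agrees with the stated minimum of 0.85. Neither figure depends on the definitions at issue.

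**Test cases for the definitions.**

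| Patient | Table 3 window | Abstract, read as in-hospital and at most 30 days | Definitions section |
|---|---|---|---|
| Dies in hospital on day 35 of a complication | counted | not counted | counted; no window given |
| Dies in hospital on day 10, not judged complication-related | counted, by the row label | counted, by the label | not counted |
| Dies at home on day 20 | not counted | not counted, unless in-hospital is taken not to apply to mortality | counted if complication-related; no window given |
| Stays 45 days | 45 days | could be cut at day 30 after surgery | 45 days |

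The first and last rows are conflicts between windows. The second is the effect of the cause restriction.

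**Does the objectivity argument cover attribution?** Whether a protocol exists is a yes/no fact about a hospital. Whether a death resulted from a complication is an inference about a patient. The argument made for the first does not carry over to the second.

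**How many deaths.** This assumes that the Background range of 1.5% to 3.13% applies to these patients.

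- All patients: 1,800 × 0.015 = 27; 1,800 × 0.0313 = 56.3.
- Table 1 has 6 control and 6 intervention group-periods of 3 × 50 = 150 patients each, so 900 per condition.
- Per condition, at equal risk: 900 × 0.015 = 13.5; 900 × 0.0313 = 28.2.
- If three deaths in one condition were attributed differently (an arbitrary number, for scale), its count would change by 3/13.5 = 22% at the low end and 3/28.2 = 11% at the high end.

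**Window and length of stay.** Under Analysis, time enters the model as a fixed effect. A trend in stay common to all hospitals is therefore handled. A change in stay caused by the strategy is not, because it coincides with the treatment indicator. Such a change is conceivable: Table 2 includes a patient card on discharge and the building of guidelines into clinical pathways. The article gives no expected stay, no infection or complication rate and no share of events after discharge, so the size of any shift cannot be calculated.

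**The case against.** The strongest points on the other side are these.

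- **The Abstract also says in-hospital.** A reader who sees only the end of its sentence might infer that follow-up to day 30 after discharge was promised and then dropped in Table 3. The full sentence does not support that: in-hospital and at most 30 days is a natural reading. This stands. The fault is inconsistent wording, which still leaves in-hospital events after day 30 and long stays undetermined.
- **Time is adjusted for.** A reader might infer that any general shortening of stay would create a false safety benefit. The fixed time effect answers that for a common trend. Only a change due to the strategy remains, and the article does not claim one.
- **Who attributes the deaths is not stated.** A reader might infer that the two unblinded researchers judge each cause of death. The article says they extract data; they may transcribe a recorded cause. This stands, but a transcribed cause is still a judgement made by staff who know the hospital's phase.
- **In-hospital counting suits the data source.** After discharge, hospital records show an infection mainly if the patient returns, so a nominal 30-day count also depends on stay. This stands and limits the remedy.
- **Some displaced events are caught elsewhere.** Readmission and reoperation within 30 days are separate outcomes, so serious events after discharge may appear there. Milder ones and deaths at home would not.
- **Low power is already conceded.** The Discussion says power may be too low for conclusions on patient safety. True, but that does not excuse a definition open to differential attribution.

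**Conclusion.** The point holds for secondary outcomes. The mortality definition brings an avoidable causal judgement into an unblinded comparison, and the stated defence does not reach it. The windows for complications, wound infections, deaths and length of stay are not stated consistently and need to be reconciled. A strategy-driven change in stay could shift the in-hospital rates.

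A bias of given size is not shown. A reader might assume a constant infection hazard with a 10% 30-day risk and compare stays of 8 and 7 days: h = −ln(0.9)/30 = 0.00351 per day, 1 − exp(−8h) = 2.8%, 1 − exp(−7h) = 2.4%, an apparent reduction of 12%. None of those inputs is in the article, and the model treats the whole stay as time after surgery although stay is counted from admission. It shows the direction of the mechanism, not its size in this trial. The death counts above likewise rest on the Background range applying here; they show only that a few reclassified deaths could matter.

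The primary outcome, the sample size and the power are unaffected.

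**What to change.** 1. Make death from any cause the mortality outcome, and report complication-related death as a supporting figure.
2. State one window for each secondary outcome, identically in the Abstract, Outcome measures, Table 3 and the definitions section.
3. Define length of stay as the full time from admission to discharge, with no cut at 30 days.
4. As a sensitivity analysis, also count complications, wound infections and deaths found up to day 30 in the records already searched for readmission, reoperation and ICU transfer.

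The first three need only changes to the text and the data-collection form. If deaths not attributed to a complication were left out in measurement rounds already extracted, vital status in those records must be checked again; the article does not say. The fourth adds some reading of records already in use. Its limits should be stated: deaths or treatment outside the hospital may be missed, and what is captured after discharge can still depend on length of stay, so it reduces the problem without removing it.

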### Data sources

Information about the processes and outcomes of perioperative care are retrospectively derived from patient medical records in the participating hospitals by two researchers (YE and GB). The first 50 patients undergoing an initial elective surgery within the measurement period and who meet the inclusion criteria are selected from the hospital databases.

To measure the structure indicators of the national indicator set, the contact person in each hospital is invited to fill out a short questionnaire on the underlying items of the structure indicators on a dichotomous scale (yes/no).

Health-care providers in the concerning hospitals are invited to respond to two different questionnaires and additional background questions on gender, medical position, and years of experience in the current function and in the current hospital. The Team Climate Inventory (TCI) [33] and the Hospital Survey on Patient Safety Culture (HSOPS) [34] are used to analyze whether team climate and patient safety culture are determinants of guideline adherence. The TCI measures the climate of the various teams of health-care providers. Good team work is essential to provide proper and safe care [35-37]. The TCI is a valid, reliable, and discriminating self-report measure of the climate of a hospital team. The TCI is based on a four-factor theory of team climate for innovation and assesses the factors, vision, participative safety, task orientation, and support for innovation in 13 subscales [33]. To measure the patient safety culture, we use the HSOPS [34,38]. The HSOPS is a valid and reliable survey for assessing the patient safety culture in hospitals. It measures 12 dimensions of patient safety culture on the basis of ideas of unsafely designed care processes or systems that increase the likelihood of the occurrence of adverse events.

### Power calculation

The key characteristic of cluster randomized trials (CRTs) is that the individual units (here: patients) within a cluster (here: hospital) are correlated, and this feature must be incorporated into power calculations and trial analysis [22]. Besides the intracluster correlation (ICC), the power calculation should also take into account the number of steps and treatment delay as the power depends on the number of steps (or measurements) and decreases by a delay in intervention effect.

We made the following assumptions: 1) nine hospitals in the Netherlands (10% of the total number of hospitals) [39] will cooperate in this study; 2) an average effect of 10%–15% increase in the process indicators (primary outcome measure) might be expected from the literature [20]; 3) baseline adherence to the guidelines is unknown, but a 15% increase from a baseline level of 50% requires the largest sample size and therefore the sample size calculated will also suffice if the baseline adherence is different from 50%; and 4) ICC is unknown but can be estimated between 0.1 and 0.3 as ICCs have shown to vary between 0 and 0.4 with a median ICC of 0.06 in other cluster randomized trials in secondary care [40]. Also, using process variables results in a comparable range and median of ICCs [40]. Based on the availability of nine hospitals, a baseline adherence of 50%, an increase of 15% by the intervention, a significance level alpha of 0.05, an ICC between 0.1 and 0.3, and four time points (three steps in the stepped design), 50 patients per cluster (equal sized) and time point are needed to reach a power of at least 0.85, using the formula of Hussey and Hughes [22]. As a result, 1,800 (50 patients × 9 hospitals × 4 measurements) patients will be included over all hospitals in the course of the trial.

### Analysis

After each measurement period, data are manually checked to identify out-of-range answers, inconsistent or missing data. Because of the hierarchical design (patients nested within hospitals), multilevel linear and logistic regression analysis will be used to compare the outcomes between treatment groups, with age, sex, the American Society of Anesthesiologists (ASA) physical status classification, and socioeconomic status (SES) as covariates. The ASA physical status classification is a five-point scale ranging from ASA 1 (healthy patient) to ASA 5 (moribund patient not expected to survive without surgery, e.g., a patient with a ruptured aortic aneurysm) [41]. Time will be included as fixed effect [22]. The association between guideline adherence and patient outcomes will also be analyzed to determine whether better adherence leads to better patient outcomes. We will use SPSS version 20.0 for data analysis. Significance for all analyses will be set at *P* < 0.05.

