## Methods/design

### Study design

Implementation of Perioperative Safety Guidelines (in Dutch: Implementatie Richtlijnen Operatieve Veiligheid (IMPROVE)) is a multicenter study in nine hospitals using an one-way (unidirectional) cross-over cluster trial design (i.e., the clusters cross over in one direction only, from control to intervention) where each participating cluster receives both intervention and control treatments consecutively, in separate periods.

A stepped wedge design is a sequential roll-out of an intervention (here: the multifaceted implementation strategy) to participants (individuals or clusters of individuals, here: groups of hospitals) over a number of time periods. All groups (hence all hospitals) start with the control situation (no IMPROVE implementation activities) at the beginning of the study. At each time point, a new group of three hospitals crosses over from the control situation to the implementation situation. Good balance of hospital characteristics (e.g., hospital type and geographical location) over the groups (of three hospitals) was achieved by matching. Each group will start the implementation phase of 4 months at a different time point, directly after one of the measurements (T0, T1, T2). The time point a group crosses over is randomized (over the groups). Randomization was computer generated by an independent statistician when recruitment of clusters was complete (Additional file 1). By the end of the study, all groups (hence all hospitals) will have received the IMPROVE implementation strategy. The intervention is never removed once it has been implemented, at least over the course of the trial.

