In our protocol, hospitals cross over from control to implementation period at three time points (Table 1). A stepped wedge design incorporates data collection in all hospitals at each time point [21,22]. The first time point corresponds to a baseline measurement where none of the hospitals have received the intervention of interest (i.e., multifaceted implementation approach). After the baseline measurement, the first group of hospitals receives the implementation strategy. After the second measurement, the next group of hospitals receives the implementation strategy, and at the third time point, the final group switches from usual care to the implementation phase, so that finally, all included hospitals have received the implementation activities. In this way, comparisons within hospitals and between hospitals will be available, making the design powerful.

**Table 1 Tab1:** **Stepped wedge design with four steps in which ‘C’ represents the control situation and ‘I’ represents the intervention phase**

**Group**	**Measurement**			
	**T0**	**T1**	**T2**	**T3**
**1**	C	I	I	I
**2**	C	C	I	I
**3**	C	C	C	I

In this study, nine hospitals are assigned into three groups of three hospitals. Data collection runs parallel for each hospital. At baseline measurement (T0), all primary and secondary outcomes will be measured per patient (*N* = 50) per hospital. In the interval between T0 and T1, implementation activities will take place in the first group of three hospitals. After the second measurement (T1), the second group of three hospitals crosses over to the intervention phase, while implementation activities continue in the first group and so on. At the final measurement (T3), all hospitals will be in the intervention phase (see Table 1).

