### Process evaluation

A process evaluation, according to Hulscher et al. [42], will be performed during and after the intervention to investigate the feasibility of the implementation strategy and to gain insight into the impact of individual implementation activities on guideline adherence. For this purpose, we will document the different implementation activities and the participation level of the health-care providers in order to determine the correlation between the implementation effect (i.e., results of our implementation strategy on guideline adherence) and compliance to the implementation strategy (i.e., degree of implementation). For this, we use the framework of Hulscher et al. for describing the key features of an implementation of change intervention [43]. In this framework, attention is paid to features of the target group, features of the implementers, and the frequency and intensity of intervention activities [43]. Based on this framework, we describe the features of the intervention as performed in detail. The process evaluation will furthermore be based on a questionnaire for the contact persons and a questionnaire for the health-care providers to measure their experience with the implementation strategy. The survey will be emailed to those who have participated in an activity. We will also determine other factors that could have influenced adherence to the perioperative safety guidelines, such as local interventions in the hospitals, audits by the IGZ, other scientific studies in this field conducted in the participating hospitals, and possible confounding factors and barriers for guideline adherence like changing registration systems in the hospitals or merging hospitals.

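### The stated model leaves no room for hospital-by-measurement variation; if such variation exists, the P<0.05 test of the strategy is anti-conservative and the stated power is optimistic

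*Protocol article*

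**What the plan says.** The Analysis section specifies the model in a few sentences. The clustering is described as follows: "Because of the hierarchical design (patients nested within hospitals), multilevel linear and logistic regression analysis will be used". Age, sex, ASA class and socioeconomic status are covariates. On time it says "Time will be included as fixed effect", citing the same Hussey and Hughes reference that supplies the power formula. The decision rule is "Significance for all analyses will be set at *P* < 0.05".

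The Power calculation section uses that formula with one ICC per calculation: nine hospitals, 50 patients per hospital and round, adherence rising from 50% to 65%, and "a significance level alpha of 0.05, an ICC between 0.1 and 0.3, and four time points (three steps in the stepped design"). It reports a power of at least 0.85.

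Under Study design, "nine hospitals are assigned into three groups of three hospitals", and the groups cross over after T0, T1 and T2. Table 3 places the rounds at -3, +4, +11 and +18 months. Under Data sources, each round takes the first 50 eligible patients of that measurement period.

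The Process evaluation section will record other influences on adherence: local interventions, inspectorate audits, other studies, and possible confounders "like changing registration systems in the hospitals or merging hospitals". The Discussion also names local safety initiatives as confounders.

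**The concern.** A hospital intercept plus common time effects treats two patients of one hospital as equally correlated whether they were operated on in the same round or up to 21 months apart. Common time effects remove only the drift that all hospitals share. A merger, a new record system or a local campaign moves one hospital in one round. Adherence is read from hospital records, so a change of registration system can move the measured value even when care does not change.

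The strategy is switched on by hospital and round, so its effect is estimated from contrasts between hospital-round cells. Variation between those cells that the model omits is missing from the standard error. At stake are the test and confidence interval for the patient-level primary indicators (STOP bundle and timely antibiotic prophylaxis), and the power that justified 1,800 patients.

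**Working it through.** **Inputs from the article.** I = 9 hospitals, T = 4 rounds, m = 50 per cell, rates 0.50 and 0.65, ICC 0.1 to 0.3 (0.06 is the quoted median from other trials), alpha 0.05 (taken as two-sided). **Assumed:** CAC of 1, 0.95, 0.9 or 0.8, since the article gives none; total variance 0.5 × 0.5 = 0.25.

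**Step 1: reproduce the plan's power.** With s² the variance of a cell mean within its hospital and t² the hospital variance,

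Var = I s²(s² + T t²) / [(IU − W)s² + (U² + ITU − TW − IV)t²].

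From Table 1, U = 18, W = 0 + 9 + 36 + 81 = 126 and V = 3 × (9 + 4 + 1) = 42. So IU − W = 36, and the multiplier of t² is 324 + 648 − 504 − 378 = 90.

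- ICC 0.1: s² = 0.225/50 = 0.0045, t² = 0.025. Var = 9 × 0.0045 × 0.1045 / (0.162 + 2.25) = 0.001755, SE = 0.0419. Power = Φ(0.15/0.0419 − 1.96) = 0.947.
- ICC 0.3: s² = 0.175/50 = 0.0035, t² = 0.075. Var = 9 × 0.0035 × 0.3035 / (0.126 + 6.75) = 0.001390, SE = 0.0373. Power = 0.980.

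Taking 0.25 as the residual variance instead gives 0.925 and 0.920. The stated lower bound of 0.85 is met under the model's own assumption, CAC = 1.

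**Step 2: add hospital-by-round variance.** Put w² = 0.25 × ICC × (1 − CAC) and reduce the hospital variance to 0.25 × ICC × CAC. The true s² becomes residual/50 + w².

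- ICC 0.1, CAC 0.9: w² = 0.0025, an SD of 5 percentage points. s² = 0.0070, t² = 0.0225. Var = 9 × 0.007 × 0.097 / (0.252 + 2.025) = 0.00268, SE = 0.0518 (0.0520 with the weights of the hospital-only model). The hospital-only model still reports about 0.0419.
- ICC 0.3, CAC 0.9: w² = 0.0075, an SD of 8.7 points. s² = 0.011, t² = 0.0675. Var = 9 × 0.011 × 0.281 / (0.396 + 6.075) = 0.00430, SE = 0.0656 (0.0659 with those weights). The model reports about 0.0373.

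**Step 3: false-positive rate** = 2[1 − Φ(1.96 × reported SE / true SE)].

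- ICC 0.1, CAC 0.9: 1.96 × 0.0419/0.0520 = 1.58, so 11%.
- ICC 0.3, CAC 0.9: 1.96 × 0.0373/0.0659 = 1.11, so 27%. It is 26% if the fitted residual absorbs a little of w².

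**Step 4: all settings.** The second figure in each rate column is from simulation under no effect with a random-intercept logistic model (z-test, 1,000 runs per setting, simulation error about 0.7 to 1.5 points). Power is for 15 points with the hospital-by-round term included (z-test).

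| CAC | Rate, ICC 0.06 | Rate, ICC 0.1 | Rate, ICC 0.3 | Power, ICC 0.1 | Power, ICC 0.3 |
|---|---|---|---|---|---|
| 1 | 5% / 5.1% | 5% / 5.0% | 5% / 4.3% | 0.95 | 0.98 |
| 0.95 | 7% / 7.0% | 8% / 7.5% | 17% / 13.3% | 0.89 | 0.80 |
| 0.9 | 9% / 8.2% | 11% / 9.3% | 27% / 19.9% | 0.83 | 0.63 |
| 0.8 | 12% / 9.7% | 17% / 13.3% | 39% / 29.9% | 0.71 | 0.43 |

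The simulation defines ICC and CAC on the latent logistic scale, which is one reason its figures run lower.

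**Step 5: does the number of hospitals matter?** With k hospitals per group, the numerator of Var carries 3k and the two denominator multipliers are 4k² and 10k². Both the reported and the true variance therefore scale as 1/k, and their ratio does not change. In simulation, nine hospitals at CAC 1 kept 4-5%, while 36 hospitals at ICC 0.1 and CAC 0.9 still gave about 8.5% (200 runs).

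**Step 6: does the extra term repair it?** In a linear model with a hospital-by-round random effect and t on 36 − 9 − 3 − 1 = 23 df, the simulated rate was about 3-7% over CAC 1 to 0.5 at ICC 0.1 and 0.3.

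**The case against.** The strongest reply is that this is a condensed article. It does not list the random terms or the degrees-of-freedom method, it does not exclude a hospital-by-measurement effect, and an analysis plan not shown here could add one. That stands as a caution. But the article is not silent: it names the nesting, makes time common to all hospitals, and cites the single-ICC formulation for both analysis and power. The term would change that stated structure and would undercut the power figure.

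A reader might also infer more than the documents support:

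- **That the P<0.05 rule gives far more than 5% false positives outright.** No CAC is given. At CAC 1 the rate is about 5%, and at CAC 0.95 with ICC 0.1 only about 8%.
- **That having only nine hospitals is the cause.** Step 5 shows it is not. Few hospitals limit degrees of freedom and power once the term is added.
- **That drift alone would make the result significant.** Even at 39%, about six in ten trials of an ineffective strategy would not reach significance.
- **That every patient-level outcome is affected to this extent.** The article gives no ICC for mortality, readmission and the other secondary outcomes, so the size there is unknown.
- **That the article predicts drift.** It lists possible influences to be recorded and gives no size. Recording them is sensible but does not correct a standard error.

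**Conclusion.** The point holds in conditional form. The analysis as described is valid at its nominal level only if hospitals do not drift differently between rounds, and the article itself names reasons why they might over 21 months. At the planned ICC of 0.1 to 0.3 and an assumed CAC of 0.95 to 0.8, the false-positive rate is about 8-39% in closed form and 7.5-30% by logistic simulation. At ICC 0.06 the closed form gives about 7-12%. Under a model that includes the variation, the power of at least 0.85 survives at CAC 0.95 only towards the lower end of the planned ICC range (0.89 at ICC 0.1, 0.80 at ICC 0.3) and is missed at CAC 0.9 and below. The mechanism is certain. The size rests on the assumed CAC and on a baseline rate of 50%.

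**What to change.** For the patient-level outcomes, state a model with random intercepts for hospital and for hospital-by-measurement, and keep time as a fixed categorical effect. Test the intervention with small-sample degrees of freedom (Satterthwaite or Kenward-Roger where the model allows, about 23). As a pre-specified check, analyse the 36 hospital-round values with hospital and round as fixed effects and a t-test on 23 df; in simulation this kept the false-positive rate at 3-6%. The hospital-level structure indicators have one value per hospital and round, so the extra term does not apply to them.

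In the Power calculation section, say that the figure of at least 0.85 assumes a CAC close to 1, and give the power for a few lower values, as in the table above.

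The cost is one extra random term and some wording. No new data are needed, and the Trial status section says that analysis had not begun. The real price is wider intervals and the lower power shown in the table.
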